## Abstract

Children with Juvenile Idiopathic Arthritis (JIA) are at a currently unpredictable risk of a blinding, often asymptomatic, co-existent eye disorder, anterior uveitis which requires prompt treatment. The unpredictability of this insidious disorder commits children with JIA to three-monthly expert clinical examinations in specialist eye centres often located far from their homes. Optical coherence tomography of the ocular anterior segment (AS-OCT) has been shown to be an acceptable, repeatable and sensitive modality for uveitis detection, but is not standard care. This feasibility randomised controlled trial (RCT) aims to inform a future full-scale RCT comparing current routine practice (expert slit lamp examination, SLE) to AS-OCT for the surveillance of uveitis in children at risk. Eighty children aged between 2 and 12 years old and diagnosed with JIA within the preceding year will be included. Participants with an existing diagnosis of uveitis, other ocular co-morbidities or those unable to complete examinations or provide informed assent will be excluded. Participants will be randomised to SLE (control) or AS-OCT (intervention) examination at a frequency consistent with the current national programme for childhood uveitis surveillance. Children in the intervention arm will also have standard examination at 6 and 12 months after study entrance. Outcomes of interest will be feasibility (recruitment and attrition rates), clinical metrics (proportion diagnosed with uveitis or other ocular disorders at 12 months after study entrance), quality of life outcomes (PedsQL), and resource use. Additionally, comparative analysis of AS-OCT versus SLE (‘gold standard’ reference testing) findings at 6 and 12 months for those in the intervention arm will provide the proof-of-concept data necessary to develop and undertake a larger scale trial. Trial registration: This trial has been registered with clinicaltrails.gov (NCT05984758).

## Introduction

Childhood uveitis is a rare but significant chronic eye condition [1]. Whist childhood onset disease accounts for approximately 1% of cases seen in adult uveitis clinics [2,3], it accounts for 10% of cases of uveitis related sight impairment amongst adults [4,5]. This over-representation is compounded by the frequent presence of multisystem disorders amongst those with childhood onset uveitis [6]. A key example is Juvenile Idiopathic Arthritis (JIA), the most common childhood inflammatory arthropathy [7]. Uveitis affecting the front section of the eye (anterior uveitis) the most common extra-articular manifestation of JIA [8]. Childhood anterior uveitis can be asymptomatic, or occur in children too young to report symptoms, so children with JIA undergo regular eye surveillance examinations every few months [9].

The strongest predictor of poor outcomes in childhood onset uveitis is the presence of established ocular structural complications at presentation, i.e., delayed diagnosis [10]. The worsening international workforce shortfall in paediatric ophthalmology is an obstacle to timely diagnosis for this population [11]. Imaging-based disease surveillance, which could be undertaken in settings across primary to tertiary care [12], would address this shortfall in capacity, providing specialist level care (potentially closer to the child’s home) to facilitate timely diagnosis and reduce the burden of uveitis related visual impairment amongst children and the adults they become.

Optical Coherence Tomography (OCT) machines have been widely adopted in secondary care and primary care settings (including high street opticians), providing high resolution images of eye structures [13]. OCT of the anterior segment (AS-OCT) to detect inflammatory cells in the eye, the hallmark of anterior uveitis, has been shown to be repeatable and highly sensitive for childhood disease [14]. Work has also been undertaken to understand the normative findings in healthy children [15]. The implementation of this potentially transformational innovation needs robust evidence on safety and effectiveness.

We aim to begin to provide the necessary high-level evidence, through a feasibility randomised controlled trial of AS-OCT versus routine clinical examination for the detection of uveitis in children at risk. This proof-of-concept study will compare imaging-based surveillance to the current approach of clinical examination (slit lamp examination-based surveillance) in the detection of uveitis in children with juvenile idiopathic arthritis The proposed study will provide the data needed to develop eligibility criteria, recruitment and retention approaches, to determine the key outcome metrics and study sample size necessary to demonstrate non-inferiority, and to inform the selection of the resource use measures needed to determine cost-effectiveness.

## Materials and methods

The proposed study has been designed in line with the SPIRIT (Standard Protocol Items: Recommendations for Interventional Trials) guidelines [16].

### Study design

This study will be a two-arm, parallel group, single site feasibility randomised controlled trial (RCT) comparing slit lamp examination-based (SLE, routine care) with AS-OCT based detection of active anterior chamber inflammation over 52 weeks in children undergoing surveillance examinations for juvenile idiopathic associated uveitis. Study participants will be children newly diagnosed (within the preceding 12 months) with JIA. The primary outcomes will be study feasibility metrics (i.e., recruitment and attrition rates). Proof of concept analyses will also be undertaken, with comparison of AS-OCT assessment to ‘gold standard’ clinical examination at 6 and 12 months.

### Setting

This will be a single site study, undertaken within a tertiary/quaternary healthcare setting: Great Ormond Street Hospital (GOSH), England, UK. Participants will be identified and recruited on attendance to routine outpatient appointments.

### Participants

Eligibility criteria comprise:

New diagnosis (within preceding 12 months) of JIAEligible for uveitis surveillance in line with national guidance (Table 1) [9]Aged between 2 and 12 years

**Table 1 pone.0316410.t001:** Guidelines for screening for uveitis in JIA by the Royal College of Ophthalmologists and the British Society for Paediatric and Adolescent Rheumatology (BSPAR).

First eye examination within 6 weeks of referral Two monthly intervals from onset of arthritis for 6 months Then 3-4 monthly eye examinations for time outlined below:	
**Age at onset**	**Length of surveillance**
Less than 3 years^a^	8 years
3-4 years^a^	6 years
5-8 years^a^	3 years
9-10 years^a^	1 year
Less than 6 years^b^	5 years
6-9 years^b^	2 years
Any age^c^	5 years

^a^- For oligoarticular JIA, Psoriatic arthritis onset and Enthesitis related arthritis (ERA).

^b^- For polyarticular, ANA + JIA onset <  10 years.

^c^- For polyarticular, ANA- JIA, onset < 7 years

Exclusion criteria comprise:

• Visual impairment or any ocular co-morbidities that would negatively impact on best corrected acuity• Developmental/learning difficulties that preclude concordance with examination/informed assent

### Study intervention *-* AS-OCT

Children randomised to the intervention arm will undergo AS-OCT imaging to detect anterior chamber inflammation. The AS-OCT images will be acquired using the Optovue RTVue OCT (8 cross-sectional scans) and the Heidelberg Spectralis OCT2 machines (anterior segment cube scan). Images will undergo manual analysis by a trained clinician to identify the presence of inflammatory cells within the anterior chamber. A later semi-automated re-analysis of acquired images will be undertaken within one week of the examination using published protocols [12,14]. Full details of image acquisition and analysis processes are available in supplemental document 1 (S1).

Imaging will be undertaken at a frequency consistent with line with national guidance (Table 1) [9]. This comprises 6 study visits in total (at Month 2 following the first visit to establish eligibility, Month 4, Month 6, Month 9, and Month 12- see Table 1 for further details). The full participant schedule of assessments is shown in Fig 1, with specific details of the study procedures shown in Fig 2.

**Fig 1 pone.0316410.g001:**
[figure not shown]
SPIRIT schedule of assessments. ^a^ Visits for those within 6 months of diagnosis: newly diagnosed: Day 1, Week 8, Week 16, Week 28, Week 40, last visit Week 52.Visits for those entering study outside the 6-month widow: Day 1, Week 13, Week 26, Week 39, Week 52.^b^ Concomitant use of a. immunosuppression or immunomodulation (and dose); any eye or visual symptoms since last visit; any other parental concerns.^c^ Measured with age-appropriate method: Cardiff cards, Thomson Kays or Thomson LogMAR in each eye separately.^d^ Heidelberg Spectralis OCT2 and Optovue RTVue anterior segment cube and single line scans.^e^ A diagnosis of new onset uveitis at any visit results in exit from the trial.

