**Fig 2 pone.0316410.g002:**
[figure not shown]
Details about the specific procedures during the intervention and control arm. * - See supplemental document 2 (S2) for specific visual acuity screening protocol.

Exit from the study will occur either at visit 7 (for participants with a new diagnosis of JIA within 6 months of entrance to study), at visit 6 (for participants whose JIA was diagnosed within 6 to 12 months of study entrance, Fig 1), or at any visit where uveitis has been diagnosed. A diagnosis of uveitis will be made clinically, using slit lamp examination. Any child within the intervention arm in whom a ‘disease positive’ AS-OCT is acquired (i.e., more than 1 hyper-reflective particle in any cross-sectional scan) will undergo a confirmatory slit lamp examination. Confirmation of uveitis will lead to a child exiting the study.

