### Study outcome measures

The main outcomes of interest are the study feasibility metrics, specifically

- The proportion of patients within the service who meet the eligibility criteria, and reasons for exclusion

- The proportion of eligible patients recruited

- The proportion of patients who withdraw due to loss of consent or are lost to follow-up

- Statistical parameters (point estimates and range/ variance) of the clinical and patient centred outcome measures

The primary clinical outcome measured (as a surrogate endpoint) will be:

- Agreement, for participants in the intervention arm, of AS-OCT findings with routine clinical examination, analysed at 6 months and 12 months milestones

Other clinical outcomes of interest will be:

- New diagnosis of uveitis

- New diagnosis of other visual/ocular problems

We shall be evaluating patient centred outcomes, specifically

- Health related quality of life (PedsQL child self-report, at 12 months and change from

baseline to 12 months)

We shall also be evaluating resource use across the feasibility study to support the design of cost-effectiveness analyses in the larger scale study.

Adverse and serious adverse events (AE/SAE) will be recorded for both the intervention and routine care arms. These events comprise (1) Development of anterior chamber inflammation; (2) development of non-sight threatening sequalae of ocular inflammation during the study period; (3) progression or disease flare of JIA; (4) development of treatment related adverse events. AE/SAE occurring in the intervention arms will be used as criteria to determine progression to a full RCT. Specifically. the progression criteria will be defined using a ‘traffic-light’ system (green – criteria met, amber – minor changes needed, red – significant changes needed).

Recruitment

-Green – > 4 recruits/month-Yellow – 2-4 recruits/month-Red – < 2 recruits/month

Adverse events (incidence of sight threatening complications in imaging-based surveillance group)

-Green/ Yellow – No cases-Red – > 1 case

Adherence to surveillance programme

-Green – > 75%-Yellow – 30-75%-Red – < 30%

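### Exit at diagnosis combined with agreement scored only at 6 and 12 months drops AS-OCT-detected interim cases from the agreement analysis but keeps missed ones

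*Protocol article*

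**What the plan says.** The exit rule appears twice. Fig 1, footnote e: "A diagnosis of new onset uveitis at any visit results in exit from the trial". The text under Fig 2 says that an intervention-arm child with a positive scan "will undergo a confirmatory slit lamp examination", and then: "Confirmation of uveitis will lead to a child exiting the study". No slit lamp examination is described for a negative scan between milestones.

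Study outcome measures gives the primary clinical outcome as "Agreement, for participants in the intervention arm, of AS-OCT findings with routine clinical examination, analysed at 6 months and 12 months milestones". The Abstract fixes when the reference test is applied to everyone in that arm: "Children in the intervention arm will also have standard examination at 6 and 12 months after study entrance".

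Fig 1 gives two visit schedules. Children within 6 months of JIA diagnosis attend at "Day 1, Week 8, Week 16, Week 28, Week 40, last visit Week 52"; the others attend at "Day 1, Week 13, Week 26, Week 39, Week 52".

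The patient-centred outcome is "Health related quality of life (PedsQL child self-report, at 12 months and change from" baseline to 12 months. Resource use is to be evaluated across the study.

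The Analysis section keeps children with a positive detection in the first 12 months in the efficacy and safety set, and follows this with a between-arm chi-square comparison. Its rule for missing outcomes names attrition. It does not mention exit at diagnosis.

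**The concern.** Whether an intervention-arm case enters the agreement analysis depends on the result of the test under evaluation. A positive scan at an interim visit, confirmed by slit lamp, removes the child before the next milestone. A false-negative scan at the same visit leaves the child in, to be scored later. The milestone table loses true positives at interim visits and loses no false negatives there.

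This matters because the Introduction and Discussion say the trial is to supply outcome metrics and a sample size for a non-inferiority trial, and the Analysis section intends to estimate how well disease is discriminated. Cases will be few in about 40 children, so losing a selected part of them weakens the estimate that the next trial most needs.

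The exit rule also cuts off the 12-month PedsQL and later resource use for the children who develop the disease under study.

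**Working it through.** The plan has no figure to reproduce: 80 is given without a derivation, and Sample size states that there is no formal power calculation. The check is an expected-value calculation on the plan's own visit weeks.

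**Inputs from the article.** Schedule A: weeks 8, 16, 28, 40, 52. Schedule B: weeks 13, 26, 39, 52. Allocation of 80 children 1:1, so about 40 have AS-OCT. Slit lamp taken as 100% sensitive (Sample size).

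**Assumptions, not in the article.** Week 28 is the 6-month milestone on schedule A. Onset is even over 52 weeks and inflammation lasts until diagnosed. AS-OCT specificity is 100%, its sensitivity *s* is 80%, 90% or 95%, and 12-month incidence is 10-30%.

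**Step 1: detectable cases first seen at an interim visit (*e*), with *m* = 1 − *e*.**
- A: (8 + 8 + 12)/52 = 28/52 = 54%; *m* = 24/52 = 46%
- B: (13 + 13)/52 = 26/52 = 50%; *m* = 50%

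**Step 2: misses that recur in the same child.** Lost share of all cases = *s·e*. Scored true positives = *s·m*. All misses, 1 − *s*, are scored. Apparent sensitivity = *s·m*/(*s·m* + 1 − *s*).

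| True *s* | A lost | A apparent | B lost | B apparent |
|---|---|---|---|---|
| 80% | 43.1% | 0.369/0.569 = 64.9% | 40.0% | 0.400/0.600 = 66.7% |
| 90% | 48.5% | 0.415/0.515 = 80.6% | 45.0% | 0.450/0.550 = 81.8% |
| 95% | 51.2% | 0.438/0.488 = 89.8% | 47.5% | 0.475/0.525 = 90.5% |

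**Step 3: misses independent between visits.** On A, onset before week 8 gives two interim chances of detection, so the lost share = [8(1 − (1 − *s*)²) + 8*s* + 12*s*]/52 = 45.5%, 49.8% and 51.9% at 80%, 90% and 95%. On B it is *s*/2 = 40.0%, 45.0% and 47.5%. Apparent per-scan sensitivity equals *s*, so there is no bias. Counting interim detections per child gives 89.1%, 95.0% and 97.6% (A) or 88.0%, 94.5% and 97.4% (B), which is a different quantity.

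Across both models and both schedules, 40-52% of cases are lost.

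**Step 4: numbers of children.** At 20% incidence there are 40 × 0.20 = 8 cases, of which 8 × 0.400 = 3.2 to 8 × 0.519 = 4.2 are lost. At 10%, 1.6-2.1 of 4 are lost; at 30%, 4.8-6.2 of 12.

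**Step 5: overall percent agreement.** Schedule A, recurring misses, *s* = 90%, 20% incidence: 0.8 cases missed and 3.88 lost. With everyone counted, 1 − 0.8/40 = 98.0%; at milestones only, 1 − 0.8/36.12 = 97.8%. The widest gap in the grid, at *s* = 80% and 30% incidence, is 1 − 2.4/40 = 94.0% against 1 − 2.4/34.83 = 93.1%.

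**Step 6: PedsQL, both arms.** If diagnosis comes at the first visit after onset, 40/52 (77%) or 39/52 (75%) of cases are diagnosed before the final visit. With 8-16 cases in 80 children (10-20% incidence) that is 8 × 0.75 = 6 to 16 × 0.77 = 12 children without a 12-month form.

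**The case against.** The strongest reply is that early cases are not lost to the trial. The Analysis section retains them in the efficacy and safety set, and new diagnosis of uveitis is an outcome of its own. That is right, and it limits the point to the agreement outcome. It does not remove it, because nothing brings the interim scan and slit lamp pair into that outcome. A separate analysis plan could do so, but the article itself fixes both the time points and the exit rule.

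A second reply is that agreement is a surrogate outcome in a feasibility trial, is not among the traffic-light criteria, and hardly moves overall. This stands. The harm is confined to positive agreement or sensitivity.

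A third is that the bias is conditional. This also stands. It needs misses that recur in the same child and inflammation that lasts to the milestone. Fig 1 records concomitant immunosuppression, so some missed inflammation could settle first.

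A reader might infer three stronger claims that the article does not support:
- **Most true positives are lost.** The rounded months under Study intervention give (2 + 2 + 3)/12 = 58%, but Fig 1's weeks give 54% and 50%. About half is the supportable statement.
- **Sensitivity is bound to read low.** With independent misses it does not.
- **The safety criterion describes mainly children who never had uveitis.** Complications present at diagnosis can be recorded at the exit visit, so only later ones are at issue. Fig 1 itself is not shown, so what is collected at exit cannot be checked.

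**Conclusion.** The concern holds for the agreement outcome. The selection follows from the article's own rules. Its size rests on even onset, inflammation that persists until diagnosis and a fully sensitive slit lamp: about half of AS-OCT-detectable cases, or 40-52% of all intervention-arm cases, go unscored. Cases first detected at a milestone visit have both tests and are unaffected.

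Loss of cases does not depend on the miss pattern; downward bias does. With recurring misses, true sensitivities of 95%, 90% and 80% read as about 90%, 81-82% and 65-67%.

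The missing 12-month PedsQL forms, 6-12 of 80, rest on an assumed incidence of 10-20%. The article gives no incidence, AS-OCT sensitivity or miss pattern, so all these figures are ranges under stated assumptions.

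The plan should be changed, but the trial's feasibility aims are not undermined. The clinical handling of a diagnosed child is not in question.

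**What to change.** 1. Keep the paired agreement at 6 and 12 months, labelled as conditional on no earlier uveitis diagnosis.
2. Add an analysis per child and per 6-month interval. A case is any uveitis confirmed by slit lamp in the interval. It is detected if a positive AS-OCT prompted the diagnosis or was present at the milestone, and missed if only the slit lamp found it. Interim AS-OCT positives that the slit lamp does not confirm count as false positives. Report the visit of first detection, so that a case missed at one visit and caught at the next is visible as delay.
3. Do not pool interim pairs scan by scan. Interim negatives have no slit lamp examination, so pooling would bring in partial verification bias in the opposite direction.
4. Reword the exit rule so that diagnosis ends the study surveillance visits but not data collection. Still collect the 12-month PedsQL, resource use and, from records, complications.

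Under recurring misses, the interval analysis returns the true sensitivity. Under independent misses it estimates detection by the programme rather than by a single scan, which is why both analyses are needed. The cost is one questionnaire and a record check for a few children, and slightly more analysis.

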**Fig 2 pone.0316410.g002:**
[figure not shown]
Details about the specific procedures during the intervention and control arm. * - See supplemental document 2 (S2) for specific visual acuity screening protocol.

Exit from the study will occur either at visit 7 (for participants with a new diagnosis of JIA within 6 months of entrance to study), at visit 6 (for participants whose JIA was diagnosed within 6 to 12 months of study entrance, Fig 1), or at any visit where uveitis has been diagnosed. A diagnosis of uveitis will be made clinically, using slit lamp examination. Any child within the intervention arm in whom a ‘disease positive’ AS-OCT is acquired (i.e., more than 1 hyper-reflective particle in any cross-sectional scan) will undergo a confirmatory slit lamp examination. Confirmation of uveitis will lead to a child exiting the study.

### Study outcome measures

The main outcomes of interest are the study feasibility metrics, specifically

- The proportion of patients within the service who meet the eligibility criteria, and reasons for exclusion

- The proportion of eligible patients recruited

- The proportion of patients who withdraw due to loss of consent or are lost to follow-up

- Statistical parameters (point estimates and range/ variance) of the clinical and patient centred outcome measures

The primary clinical outcome measured (as a surrogate endpoint) will be:

- Agreement, for participants in the intervention arm, of AS-OCT findings with routine clinical examination, analysed at 6 months and 12 months milestones

Other clinical outcomes of interest will be:

- New diagnosis of uveitis

- New diagnosis of other visual/ocular problems

We shall be evaluating patient centred outcomes, specifically

- Health related quality of life (PedsQL child self-report, at 12 months and change from

baseline to 12 months)

We shall also be evaluating resource use across the feasibility study to support the design of cost-effectiveness analyses in the larger scale study.

Adverse and serious adverse events (AE/SAE) will be recorded for both the intervention and routine care arms. These events comprise (1) Development of anterior chamber inflammation; (2) development of non-sight threatening sequalae of ocular inflammation during the study period; (3) progression or disease flare of JIA; (4) development of treatment related adverse events. AE/SAE occurring in the intervention arms will be used as criteria to determine progression to a full RCT. Specifically. the progression criteria will be defined using a ‘traffic-light’ system (green – criteria met, amber – minor changes needed, red – significant changes needed).

Recruitment

-Green – > 4 recruits/month-Yellow – 2-4 recruits/month-Red – < 2 recruits/month

Adverse events (incidence of sight threatening complications in imaging-based surveillance group)

-Green/ Yellow – No cases-Red – > 1 case

Adherence to surveillance programme

-Green – > 75%-Yellow – 30-75%-Red – < 30%

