### Sample size

As a feasibility study, there is no formal power calculation based on clinical non-inferiority for a diagnostic intervention [17]. To ‘quantify’ and assess the concept that imaging-based surveillance is not inferior to clinical slit-lamp examination in the detection of active anterior uveitis in children at risk, the starting point will be that that SLE findings (assumed to be abnormal in 100% of children with an active anterior uveitis) and AS-OCT findings will concord in at least 95%.

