### Randomisation and allocation

Coordinated registration and allocation of participant trial numbers will be used. Participants will be allocated using computer-generated permuted block randomisation into one of two arms (1:1, block size = 4) stratified by age (8 and under, over 8). This will be undertaken centrally by the coordinating trial team using Sealed envelope (www.sealedenvelope.com). Allocation will not be concealed, and participants cannot be masked to their allocation to routine (slit lamp examination) or imaging-based surveillance (AS-OCT) examinations.

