### Data collection and processing

Data will be entered into electronic data collection forms (DCFs) using the REDCap platform, with collection undertaken during study visits by research associates or clinicians and reviewed for completeness by an investigator. Alongside the data collection forms, optical coherence tomography (OCT) images will be collected from participants.

To limit data missingness, the following approaches will be used

- Validation rules within the REDCap form (i.e., form submission will not be permitted if data entry points have not been completed)

- Incoming data review monthly by the study team and screening committee to identify missingness, and any patterns of/ reasons for missingness within the study dataset

- Exclusion from outcomes analysis of participants lacking a full dataset for more than two consecutive study visits

Patient data will not be transferred to any party not identified in this protocol and will not to be processed and/or transferred other than in accordance with the patients’ (parent’s) consent. Direct access to the data will be granted to authorised representatives from the Sponsor, host institution and the regulatory authorities to permit study-related monitoring, audits and inspections. This trial will collect personal data (e.g., participant names), including special category personal data (e.g., participant medical information) and this will be handled in accordance with all applicable data protection legislation. Data (including special category) will only be collected, used and stored if necessary for the trial. The database and randomisation system will be designed to protect patient information in line with the GDPR. All documents will be stored securely and only accessible by study staff and authorised personnel.

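### A child who keeps attending but repeatedly gives no usable AS-OCT is not clearly penalised and may be dropped, so imaging-arm agreement may describe only scannable children

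*Protocol article*

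**What the plan says.** Four statements in the protocol article bear on a child who attends but cannot be scanned.

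- **Attrition** (Study outcome measures): "The proportion of patients who withdraw due to loss of consent or are lost to follow-up". A child who attends every visit is neither.
- **Missing outcomes** (Analysis): these are scored as adverse, with the qualification that the missingness comes from attrition.
- **Exclusion for incomplete data** (Data collection and processing, in the list of ways to limit missingness): "Exclusion from outcomes analysis of participants lacking a full dataset for more than two consecutive study visits". The rule names no arm and makes no exception for a child who attended.
- **Primary clinical outcome** (Study outcome measures): "Agreement, for participants in the intervention arm, of AS-OCT findings with routine clinical examination, analysed at 6 months and 12 months milestones". No denominator is stated for a milestone without a usable scan.

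Neither the listed feasibility metrics nor the three traffic-light criteria name scan completion. Adherence to surveillance has thresholds (green above 75%, yellow 30% to 75%, red below 30%), but the article does not say whether attending or completing the allocated examination counts.

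The article also differs with itself on who is enrolled. The Abstract says "those unable to complete examinations or provide informed assent will be excluded", whereas the Participants section limits this to inability arising from developmental or learning difficulties.

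**The concern.** Failure to obtain a usable AS-OCT is the failure most specific to this intervention, and enrolment starts at age 2. The stated rules treat two kinds of loss differently. A family that leaves has its missing outcome scored as adverse. A child who stays but cannot be scanned is not clearly covered by that rule, and after three incomplete visits in a row can be taken out of the outcomes analysis.

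The trial is meant to supply eligibility criteria, outcome metrics and sample-size inputs for a non-inferiority trial. If agreement and imaging-arm outcomes come only from children who can be scanned, those inputs may not carry over to a population that includes children who cannot. The adherence criterion has a related gap: it could read green on attendance while fewer children complete the examination being tested.

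**Working it through.** **No sample-size figure to reproduce.** The Sample size section says "there is no formal power calculation based on clinical non-inferiority for a diagnostic intervention" and gives no alpha, power or margin. The total of 80 (Abstract) is not disputed here.

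**Inputs**
- Imaging-arm size: 80 children allocated 1:1 (Abstract; Randomisation and allocation), so 80/2 = 40.
- Working concordance: "AS-OCT findings will concord in at least 95" per cent (Sample size), described there as a starting point.
- Scan-failure rate: not in the documents. Assumed 5%, 10% and 20%, that is 2, 4 and 8 of 40.
- Assumed: all 40 are present at the milestone. Uveitis exits and attrition would lower this.

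**Step 1: how the rules apply to one child.** Take a child who attends throughout and gives no usable scan at three visits in a row.

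| Rule | Effect on this child |
|---|---|
| Attrition metric | Not counted; consent stands and the child is not lost |
| Missing scored as adverse | Not clearly applied; the missingness is not due to attrition |
| Exclusion for incomplete data | May apply, if a full dataset requires the scan |
| Agreement outcome | No rule for a milestone without a finding |

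The Fig 1 footnote gives five or six visits, so the exclusion needs three in a row out of five or six. Isolated failures do not trigger it.

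**Step 2: agreement on the two denominators.** Let s = 40 minus failed scans, with one discordant result among the s.
- Gradable only: (s − 1)/s.
- All due a scan, failure counted as not concordant: (s − 1)/40.

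| Assumed failure | s | Gradable only | All due a scan | Gap (points) |
|---|---|---|---|---|
| 5% | 38 | 37/38 = 97.4% | 37/40 = 92.5% | 4.9 |
| 10% | 36 | 35/36 = 97.2% | 35/40 = 87.5% | 9.7 |
| 20% | 32 | 31/32 = 96.9% | 31/40 = 77.5% | 19.4 |

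The second figure is the first multiplied by the gradable proportion; at 10%, 35/36 × 36/40 = 35/40.

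**Step 3: the same check at about 95% concordance among scanned children.** Concordant count = 0.95 × s, rounded; Wilson 95% intervals.

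| Assumed failure | Gradable only | All due a scan (95% CI) |
|---|---|---|
| 0% | 38/40 = 95.0% | 38/40 = 95.0% (83.5 to 98.6) |
| 5% | 36/38 = 94.7% | 36/40 = 90.0% (76.9 to 96.0) |
| 10% | 34/36 = 94.4% | 34/40 = 85.0% (70.9 to 92.9) |
| 20% | 30/32 = 93.8% | 30/40 = 75.0% (59.8 to 85.8) |

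The gaps are again about 5, 9 and 19 points. At 5% the gap is small against the sampling error. At 10% the all-due interval lies below 95%.

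**Step 4: adherence.** Completed examinations = attendance × (1 − failure rate). With an assumed 90% attendance:
- 10% failure: 0.90 × 0.90 = 81%, green on either reading.
- 20% failure: 0.90 × 0.80 = 72%, yellow, against 90% (green) on attendance.

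With an assumed 95% attendance and 20% failure, 0.95 × 0.80 = 76%, still green. The colour changes only for some combinations.

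**The case against.** A reader might infer that failed scans are counted nowhere. The article does not support that. Data collection and processing provides a monthly review of missingness and its reasons. The Analysis section explores missing data against baseline characteristics and names age. The undefined adherence criterion may already require a completed examination, and reasons for ineligibility are a listed metric. What remains is that none of these is a named scan-failure outcome, and none overrides the exclusion.

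A reader might also infer that only the imaging arm loses its failures. The exclusion is worded for all participants, and a young child may fail a slit lamp examination too; no failure rate is given for either test. Only AS-OCT failure is confined to the imaging arm.

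It can fairly be said that the attrition metric is not wrong. Withdrawal plus loss to follow-up is the ordinary meaning, and a child who attends is retained. Folding test failure into attrition would blur the retention estimate that the next trial needs. This objection stands.

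Agreement among paired readings is a valid estimate for scannable children if its denominator is shown, and counting failures as non-concordant is one convention among several. This also stands, and is a reason to report both rather than replace one with the other.

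The exclusion does not define a full dataset as including a gradable scan, and two OCT devices are used, so failure on one is not necessarily failure of the visit. Supplement S1 is not shown and may define gradability. That would narrow the problem, but would not by itself change the exclusion or the limit on missing-as-adverse scoring.

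**Conclusion.** The concern holds as a conditional risk. As written, the rules can remove attended-but-unscannable children without clearly penalising the missing result, so agreement and imaging-arm outcomes may be more favourable than they would be for all children due a scan.

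The gap is about 5, 10 and 19 points at assumed failure rates of 5%, 10% and 20%, with 40 children and one discordant result. It rests on three assumptions: the failure rate, agreement being computed only on gradable scans, and failures being regarded as non-concordant on the wider denominator.

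The article does not show that feasibility and agreement are overstated. No failure rate is given, and agreement is not a progression criterion. Nor do two failed scans alone breach the 95% starting point: 38/40 = 95.0% still meets it, and a discordant result as well is needed to fall below. The risk is still worth removing before analysis, because whether young children can be scanned is part of what a feasibility trial should measure.

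**What to change.** 1. State that the exclusion for incomplete datasets does not apply to children who attended but could not be scanned. Keep them in their randomised arm and use their 6- and 12-month slit lamp results, which the Abstract already schedules for the imaging arm.
2. Report agreement at 6 and 12 months twice: among gradable scans, and among all children due a scan with failed scans as not concordant.
3. Add the proportion of scheduled AS-OCT visits with a gradable scan as a feasibility metric, by the randomisation age strata (8 and under, over 8). For the adherence criterion, report attendance and completed allocated examination separately.
4. Leave the attrition definition unchanged.
5. Reconcile the Abstract with the Participants section on whether inability to complete examinations is an exclusion in itself.

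The cost is wording and a few extra summaries from data already collected. Agreement and adherence figures may look less favourable.
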